**Main study - Sample size rationale:**

| **Cohort** | **Male** | **Female** | **TOTAL** |
| --- | --- | --- | --- |
| Recent survivors  (0-3 months post-symptom onset) | 120 | 120  • including menstrual blood samples, as available  • including breast milk samples if any lactating women are enrolled | 240 |
| PLHIV |  |  | 30 |
| **TOTAL** |  |  | **270** |

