**1. Detailed description of the project**

**1.1 Background information and rationale**

The epidemic of Ebola virus disease (EVD) that began in 2014 in West Africa has been unprecedented in scale and duration. As of August 2, 2015, there have been over 27,862 reported cases and over 11,000 deaths, in the three most affected countries: Sierra Leone, Guinea, and Liberia. These case counts may underestimate the true case numbers and deaths due to underreporting. Recently, reported incidence has been falling in all three countries, but transmission and new cases continue to occur. As of August 2, 2015, a total of

7 cases had been reported in the previous 21 days in Sierra Leone, 27 in Guinea, and 0 in

Liberia. To date, the case fatality rate is estimated to be between 53 and 64% in the 3 countries. The precise number of survivors is unknown, but is expected to be in the thousands. Survivors are released from Ebola treatment units (ETUs) with a discharge certificate after two tests for EBOV in the blood have been negative by reverse transcription polymerase chain reaction (RT-PCR).

Anecdotal reports suggest that some new cases might be occurring from sexual transmission of the virus between EVD survivors and their sexual partners. In addition to concerns about semen and vaginal fluid, concerns exist regarding the unknown persistence of EBOV in other body fluids of survivors (e.g., saliva, sweat, tears, urine, rectal swabs, and breast milk), and their potential as a source of ongoing transmission; the literature does not rule out these possibilities.

After clinical improvement and elimination of viremia, limited data exist concerning EBOV clearance, persistence, and shedding during convalescence, including the relation to IgM and IgG response. It has been reported that EBOV can be detected in seminal fluids of a convalescent man at 82 days after onset of symptoms. Knowledge is scarce in relation to what influences Ebola persistence in body fluids following recovery from Ebola. It has been stipulated that sexual activity involving ejaculation may decrease viral load in semen, and likewise may influence results of test for detection. The putative association has been discussed in the literature, but has not been further examined so far.

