***1.2.4 Specific objectives of Main study:***

**Main study: Persistence of Ebola virus in semen, vaginal secretions and other body fluids among EVD survivors**

• In 1st /baseline specimen samples, to assess period prevalence of:

a) presence of Ebola RNA detected by RT-PCR

b) of live Ebola virus detected by culture/viral isolation in: i) semen, ii) vaginal swab, iii) rectal swab, iv) sweat, v) urine, vi) saliva, and vii) tears, viii) menstrual blood and ix) breast milk, if applicable.

• To assess the maximum duration of:

a) any Ebola ribonucleic acid (RNA) detected by RT-PCR and

b) of live Ebola virus detected by culture/viral isolation in: i) semen, ii) vaginal swab, iii) rectal swab, iv) sweat, v) urine, vi) saliva, and vii) tears, viii) menstrual blood and ix) breast milk if applicable.

• To analyse the survival function, including survival probabilities (probabilities of virus persisting) at key time points, using RT-PCR and viral isolation results among individuals with specimens that are positive by RT-PCR at the baseline visit, and with subsequent specimens collected until RT–PCR and virus isolation are confirmed negative.

• To inform maximum duration of persistence in semen and to estimate a period prevalence of viral persistence in semen of survivors 12-15 months post disease onset. (‘Tail-end cohort’).

• Describe concordance between RT-PCR (including CT-values) and viral culture results for EBOV in these body fluids.

• To analyze viral persistence in relation to host factors (socio-demographics, behavioral variables, Ebola disease course and severity, other diseases including HIV, reproductive health including pregnancy, and humoral immune response.)

- To describe outcomes of pregnancy and delivery in pregnant participants (detailed in annex to the protocol)

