**Main study**

All adult men or women (18 years or above), discharged from an ETU during relevant time periods (please see sample distribution), holding a certificate of recovery, are eligible.

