**Main study sample size:**

The following is the rationale for estimating the sample size needed for body fluids other than semen, when hypothetically the prevalence of persistence will be low and approaching zero, and when there is a wish to ‘rule out’ the possibility of viral persistence at a given time point by way of independent specimen provided by participants at baseline. The below sample size calculations for a zero prevalence estimate hence refer to estimating a population proportion at a certain point (or period) in time (i.e. at a specified time since EVD onset).

For the primary outcome of live virus isolated in tissue culture, even one positive (live EBOV virus) outcome is of interest; as such a finding would be expected to have important implications for guidance to future caregivers, patients, and their families. Similarly, we would not want to conclude that there is no probability of persistent live EBOV virus in the fluids we test if, in reality (within the larger population), there is. Therefore, the primary power calculation of interest is the degree of confidence we can have in a null (no positives) result from our tissue culture testing. In other words, we need to know the upper confidence limit for a calculated proportion of 0% in our study.

There are several ways to calculate an upper bound for a 95% confidence interval for a 0% finding. The rule of thumb for the upper bound is 3/N, where N is the number of specimens tested.6 This method is accurate when the sample is sufficiently large. Calculating the upper bound precisely requires use of the binomial distribution. The table below lists the upper bounds for a 1-sided 95% confidence interval estimated using Stata SE V12.1

Numerator 0 0 0 0

Denominator 50 100 200 300

Upper bound 7.1% 3.6% 1.8% 1.2%

Lower bound 0% 0% 0% 0%

In line with the above, based on the assumption of a 1st sample period prevalence (0-3 months) of viral persistence in body fluids other than semen, approaching zero we aim for a sample of 100 total participants (50 men and 50 women), adding an additional 20% of participants to account for potential drop-out. We would then arrive at a 95% confidence interval in gender specific sub-analysis of 0-7.1% and if all specimens are negative for both sexes a collapsed group analysis with a 95% CI of 0-3.6%.

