**1. 60 men and 60 women (50+20% drop-out) should hence be included, in each of the study sites (Freetown and Porto Loko.)**

In order to maximize the possibility of detecting virus RNA in body fluid specimens, the lag time since symptom onset should be pushed towards recent survival (3 months post discharge or less). If male or female survivors with <= 3 months since discharge cannot be identified, the lag time may need to be postponed until 6 months post discharge. Male survivors from the pilot study may be invited for this purpose, for additional body fluid testing, but would need to be drawn from a random list of pilot participants, giving semen negative men an equal probability as semen positive to participate.

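### The zero-event precision stated for 0-3 months needs 100 evaluable survivors, which the protocol's own case figures do not support; the window's time origin and the tail-end cohort also need reconciling

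*Combined protocol and SAP*

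**What the plan says.** The text under Main study sample size treats the upper limit for a zero result as the power calculation of interest. It ties that limit to the first-sample period prevalence at 0-3 months: "we aim for a sample of 100 total participants (50 men and 50 women"), plus 20% for drop-out. The resulting intervals are 0-7.1% per sex and 0-3.6% pooled.

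The table under Main study - Sample size rationale has one row besides PLHIV: recent survivors, "0-3 months post-symptom onset", 120 men and 120 women.

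Item 1 below the table measures recency differently: "the lag time since symptom onset should be pushed towards recent survival (3 months post discharge or less"). If such survivors cannot be found, "the lag time may need to be postponed until 6 months post discharge", and pilot men may be invited. Item 2 (menstrual blood) has a similar fallback, also counted from discharge.

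Section 1.1 gives the only recent incidence, as of 2 August 2015: "7 cases had been reported in the previous 21 days in Sierra Leone". It adds that incidence has been falling, that counts may be under-reported, and that "the case fatality rate is estimated to be between 53 and 64" per cent. Section 8 places main-study recruitment in Fall 2015, December 2015 and January 2016.

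Section 1.2.4 also sets a tail-end objective, to "estimate a period prevalence of viral persistence in semen of survivors 12-15 months post disease onset". The main-study enrolment paragraph makes eligible those "discharged from an ETU during relevant time periods (please see sample distribution"), but the table has no 12-15 month row.

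**The concern.** The 0-3 month limit is the only precision the plan offers for body fluids other than semen, and results are meant to update counselling and public recommendations. If far fewer than 100 participants fall in the window, a run of negatives is much weaker evidence than the plan states. The timed positives that Section 1.1 cites for other fluids are all early: breast milk at 7 and 15 days, conjunctival fluid 22, urine 26, rectal swab 29, vaginal secretions 33 and sweat 40 days. If the early window is thinly filled and the result is read against the stated limit, it could reassure falsely.

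Two textual gaps add to this and need no extrapolation. The window is counted from symptom onset in the table but from discharge in items 1 and 2. The 12-15 month objective has no row in the table that defines eligibility.

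**Working it through.** **1. The plan's own limits.** The exact binomial upper limit for 0 of n is 1 - a^(1/n).
- With a = 0.025: n=50 gives 7.11%, n=100 gives 3.62%. These match the plan.
- With a = 0.05, as the table's one-sided 95% label implies: 5.82% and 2.95%. These do not match. The printed limits are two-sided 95% limits, so a = 0.025 is used below.
- Enrolment: 50 × 1.2 = 60 per sex per site; × 2 sexes × 2 sites = 240. The quoted precision itself needs only 50 per sex and 100 in all.

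**2. Supply of 0-3 month survivors.**
- Rate: 7/21 = 0.333 cases per day (Section 1.1), held constant. This is an assumption.
- Window: 3-month look-back plus 5 months of recruitment, taking Fall as September to November (an assumption). This runs June 2015 to January 2016, about 243.5 days.
- Cases: 0.333 × 243.5 = 81.2.
- Survival: 1 - 0.64 = 0.36 to 1 - 0.53 = 0.47 from the stated fatality. From the crude counts in Section 1.1 (over 27,862 cases, over 11,000 deaths), 1 - 11,000/27,862 = 0.605.

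| Survival | Survivors, all ages | Pooled limit, 0 positives | Approx. per sex (n) | Limit per sex |
|---|---|---|---|---|
| 0.36 | 29 | 11.9% | 15 | 21.8% |
| 0.47 | 38 | 9.3% | 19 | 17.6% |
| 0.605 | 49 | 7.3% | 24-25 | about 14% |
| Plan | 100 | 3.6% | 50 | 7.1% |

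With a = 0.05 the pooled limits at n=29 and n=49 are 9.8% and 5.9%, against 2.95% at n=100. The conclusion is the same.

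**3. Rate needed for 100 survivors.** Cases needed: 100/0.36 = 278, 100/0.47 = 213, 100/0.605 = 165. Over 243.5 days that is 24.0, 18.3 and 14.3 per 21 days, or 3.4, 2.6 and 2.0 times the stated rate.

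**4. If only the undocumented early weeks were higher.** About 41 days, from 1 June to mid-July 2015, precede the quoted count. With the other 202.5 days at the stated rate (67.5 cases), those 41 days would have to supply 165 - 67.5 = about 98 to 278 - 67.5 = about 210 cases. That is 50-108 per 21 days.

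**5. The fallback.** A 6-month lag plus 5 months of recruitment is about 334.8 days, giving 111.6 cases and 40, 52 or 67 survivors. Even if all were pooled, the limits would be 8.8%, 6.8% and 5.4%. Those beyond 3 months do not belong in a 0-3 month bound in any case. The lag is counted from discharge, so the onset window is somewhat longer than this; the documents do not give the onset-to-discharge time.

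**The case against.** - **One 21-day count is stretched over 8 months.** This stands. Incidence before mid-July and after 2 August 2015 is not given, and under-reporting is admitted. A reader might infer that the precision cannot be delivered; the documents support only that it looks unattainable on their figures. In the other direction, the supply estimate counts all ages, the whole country and full consent, and holds a falling rate constant.
- **240 is the wrong comparator.** This stands for precision. A reader might set 29-38 survivors against 240 places, but 240 is the enrolment target. The quoted limits need 100.
- **Strata are already planned.** Section 7 lists period prevalence at 0-3 months, >3-6 months and so on, and counts persistence from symptom onset, also presenting it from discharge. A reader might infer that later recruits will be reported as 0-3 month evidence. No passage says so. It is a risk, because no precision is stated for any later stratum and no rule confines the bound to participants inside the window.
- **The tail-end cohort has possible sources.** A reader might infer that this objective gets no participants. That goes too far: pilot men may be merged with the main cohort, and Section 2.1.1 names tail-end men among the considerations for a second site. What stands is the missing row or link in the table used for eligibility.
- **The shortage is foreseen, and pilot men can help.** Some of them could still be within 6 months in Fall 2015, so the fallback can fill places. Men beyond 3 months from onset still add nothing to the 0-3 month limit.

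**Conclusion.** The point holds in this form. The 0-3 month precision is not supported by the protocol's own figures and looks unattainable on them: about 29-49 survivors against 100 needed, with zero-event limits roughly two to three times those stated, both pooled (7.3-11.9% against 3.6%) and per sex (14-22% against 7.1%). This rests on a constant 7 cases per 21 days, an assumed 8-month onset window, survival of 36-60.5% and an even split by sex. Incidence averaging 2.0-3.4 times the quoted rate would supply 100 survivors of all ages, and the documents do not exclude it. They describe a falling rate, however, and not all of those survivors would be eligible adults who enrol.

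The mismatch between onset and discharge, and the 12-15 month objective without a row in the eligibility table, stand on the text alone.

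**What to change.** 1. Under Main study sample size, state the expected number of participants at 0-3 months, with the assumptions behind it, and restate the per-sex and pooled zero-event limits at that number.
2. State that the 0-3 month bound is computed only on participants within 0-3 months of symptom onset at first sample, and that the limit on achieved n is reported separately for each time stratum already named in Section 7.
3. Define the window in the cohort table and in items 1 and 2 from one origin, symptom onset, as Section 7 does. Bring the specimen projection tables, which say 1-3 months, into line.
4. Add a row or cross-reference for the 12-15 month semen tail-end cohort to the cohort table, and name its source (merged pilot men or second-site recruits).

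The 240 places need not be recut into fixed strata. That would fix numbers for a 0-3 month group that may not be fillable and take places from the sample for other fluids.

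The cost is rewording, with no added participants. The downside is that the stated 0-3 month precision becomes less favourable.

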**1. 60 men and 60 women (50+20% drop-out) should hence be included, in each of the study sites (Freetown and Porto Loko.)**

In order to maximize the possibility of detecting virus RNA in body fluid specimens, the lag time since symptom onset should be pushed towards recent survival (3 months post discharge or less). If male or female survivors with <= 3 months since discharge cannot be identified, the lag time may need to be postponed until 6 months post discharge. Male survivors from the pilot study may be invited for this purpose, for additional body fluid testing, but would need to be drawn from a random list of pilot participants, giving semen negative men an equal probability as semen positive to participate.

**2. Menstrual blood:**

For the purpose of collecting menstrual blood, a sample of 50 women would be needed, if the prevalence approaches zero, in order to arrive at a 95% CI 0f 0-

7.1%. All of the 60 women of the main study will be informed and invited to provide specimen from the first or initial days of the menstruation period. It is expected that not all of these women would be regularly menstruating and able or willing to participate. Through the same channels as above, women survivors, of preference up to 3 months post-discharge, else up to 6 months, will be invited to cover the sample size needed.

**3. HIV positive Ebola survivors’ sub-cohort:**

The expected number of PLHIV who have also survived Ebola is supposedly low. NETHIPS has done an estimate based on their network, by district, suggesting some 30 PLHIV Ebola survivors in total in the country. NETHIPS and other relevant networks and resources will be used to invite participants; these participants are most likely already on ART. HIV Counselors will also be engaged to encourage their clients who are EVD survivors to participate in the study; these participants may not yet be on ART. All identified PLHIV who have survived Ebola would be included in this sub-cohort, up to a maximum of 50 men and 50 women, irrespective of time since discharge for Ebola, and also from all geographical regions, as feasible. These PLHIV will constitute a separate sub-cohort. If any study participant recruited for the main cohort is presenting with a known HIV infection or is diagnosed with an HIV infection within the study, s/he will be included in the PLHIV sub- cohort and will be replaced in the main study cohort.

**2.2 Admission procedure**

**Main study**

1. For all patients recruited, the study will be explained and informed consent obtained and signed (see Section 2.1.2 on patient enrollment and Appendix 1; see Ethics section below). Contact information will be collected.

2. At the first visit, the participant will be assigned an individual personal ID number for the study. A study ID card should be given to the patient with his/her ID number. In a secure electronic record, linking sex, age, name, chiefdom, ETU case report form (CRF) number and survivor certificate numbers (if available) to the ID number should be kept safely and only used for returning study participants who lost their ID card. A designated study team member will record information on exposure to experimental treatment that was captured in the participants corresponding ETU CRF where available).

3. A base-line interview with the survivor by way of a standardized questionnaire (refer to Annex 1) including questions on socio-demographics, symptom debut, co- morbidity, house-hold members, menstruation, breast feeding and current sexual partners will be done at the baseline and at any follow-up visits. The interview will be conducted by a trained interviewer from the MSWGCA. The questionnaire will be available in English, Krio and any local languages in the catchment area.

4. After the administration of the questionnaire, there will also be the1st sampling of body fluid specimens. Specimens of semen and urine will be self-collected by the participants. Rectal swab, vaginal secretions, and breast milk specimens will also be self-collected or collected with assistance from the lab technician or nurse. Sweat, saliva, and tears will be collected by the lab technician or nurse. A venous blood sample will be drawn to enable analysis of EBOV specific IgM and IgG antibody titers in serum. Procedures for specimen collection will be explained by study staff (see operations manual) and specimen collection will be completed in a secure, private space in the study clinic using appropriate infection control precautions.

5. The participant will be offered EVD test results from prior study visits and standardized counselling on Ebola transmission risks by trained personnel of the same sex as the participant. Participants will be provided with a 5-week supply of condoms (approximately 35 condoms). Women with positive breast milk will be given infant formula at every visit. Participants will be provided with a financial incentive for participation in each study visit (Section 12.4). Additionally, the follow-up visit for provision of test results will also be scheduled and all contact information will be reviewed again.

6. Participants will be given the option to receive an HIV test and pre and post-test counseling. All HIV positive patients will be referred for HIV follow-up care as per national guidelines. Participants who are known to be HIV-infected will be offered counselling on living with HIV and linkage to care via the Sierra Leone national AIDS control program if they are not currently engaged in HIV care.

7. Participants who are HIV positive will be included in the PLHIV sub-cohort. A confirmatory HIV test will be performed at the time of the first visit.

8. Women will be offered pregnancy testing, and if positive they will be referred to antenatal care (ANC), pending on gestational age and needs, care will be offered in line with national guidelines for Ebola survivors. If a woman states that she knows she is pregnant, a confirmatory pregnancy test will be performed.

9. Participants will be offered their RT-PCR test results at the subsequent study visit, 2 weeks after the current one.

10. Risk reductionounseling about avoiding potential transmission of Ebola will be provided to all participants as part of pre-test and post-test sessions, and their test results will be provided along with individualized counseling messages.

**Specimen Collection Main study**

1. Specimen collection will take place in designated areas of the study clinic, in a special room designated for this purpose. The study technician will label and mark all specimen containers before collecting, with the participant’s personal ID number, study name, visit number, date, specimen description and name of clinic. All specimen collection will follow guidelines; see further details in operations manual.

2. Blood, sweat, tears and saliva will be collected by a trained healthcare worker. Breast milk, vaginal swab (for vaginal secretions and menstrual blood) and rectal swab can either be self-collected, or collected by a gender appropriate, trained healthcare worker. Semen and urine will be self-collected by the participant using low- literacy illustrated instruction cards and detailed verbal instructions from the trained healthcare worker. Specimens placed on a designated counter in the private room. A trained healthcare worker (well informed of the SOP and trained in infection control procedures and wearing adapted personal protection equipment (face mask, apron, gloves, and boots) against potential contaminated fluids) will then enter the room and seal the container with the specimen respecting all infection control procedures.

3. Serum will be collected by a trained healthcare worker, the procedure aligned with standard practice for infection control.

4. For male participants, urine should be collected prior to semen specimen collection to prevent the risk of contamination.

5. Collection of the different specimens will follow standard operating procedures (Outlined in operations manual).

Specimen projections by visit, MEN 1-3 months post EVD symptom onset:

|  | **Blood** | **Semen** | **Saliva** | **Tears** | **Urine** | **Sweat** | **Rectal** | **TOTAL** |
| --- | --- | --- | --- | --- | --- | --- | --- | --- |
| **Visit 1** | 120 | 120 | 120 | 120 | 120 | 120 | 120 | 840 |
| **Visit 2** | 120 | 120 | 120 | 120 | 120 | 120 | 120 | 840 |
| **Visit 3** | 120 | 120 | 120 | 120 | 120 | 120 | 120 | 840 |
| **TOTAL** | 360 | 360 | 360 | 360 | 360 | 360 | 360 | 2520 |

Specimen projections by visit, WOMEN 1-3 months post EVD symptom onset:

|  | **Blood** | **Vaginal OR Menstrual Blood** | **Saliva** | **Tears** | **Urine** | **Sweat** | **Rectal** | **Breast Milk** | **TOTAL** |
| --- | --- | --- | --- | --- | --- | --- | --- | --- | --- |
| **Visit 1** | 120 | 120 | 120 | 120 | 120 | 120 | 120 | ? | 840 |
| **Visit 2** | 120 | 120 | 120 | 120 | 120 | 120 | 120 | ? | 840 |
| **Visit 3** | 120 | 120 | 120 | 120 | 120 | 120 | 120 |  | 840 |
| **TOTAL** | 360 | 360 | 360 | 360 | 360 | 360 | 360 |  | 2520 |

Projected number of samples from men and women for:

• First 6 weeks of study: 5040 specimens

• 4 month period: 3840 specimens

• Assuming approximately 6 participants per day with an average of 7 specimens per participant, 42 specimens per day / 240 specimens per week

• Handling and transport will follow routines for safety and transport as outlined in operations manual.

• The examination room will be cleaned after use by sanitation workers (hygienist) wearing standard protection against potential contaminated fluids.

